#### Randomisation

Following the baseline interview, an independent researcher randomises participants to either the intervention or control group. A permuted block randomisation procedure is utilised (e.g., Altman et al., 2001) whereby participants are allocated to the intervention or control group through the use of a randomly generated number. The permuted blocks are organised in groups of four (e.g., AABB, ABAB, BBAA) the details of which are not known by investigators involved with the administration of the trial. A random number sequence is generated which indicates the block of four conditions to be utilised for the following four cases. The use of the permuted block randomisation process ensures that intervention group numbers are balanced at the end of each block and is thus the recommended process in studies with smaller samples (i.e., n < 100).

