## Method/design

### Study design

The study design is a randomised control trial where the intervention is being compared to treatment as usual. Enrolment is conducted at Odyssey House Victoria (OHV), an addiction treatment facility located in Melbourne, Australia. Enrolment commenced June 2010 and is ongoing. All procedures are conducted in accordance with the Australian Code for the Responsible Conduct of Research and were approved by the Deakin University Human Research Ethics Committee.

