#### Initial screening

Intake assessments are conducted at OHV in order to determine client suitability for treatment. As part of the standard intake assessment clients complete the self-report version of the Liebowitz Social Anxiety Scale – Self-Report version (LSAS [54]). If the client meets eligibility for the study the intake team provides them with information about the study and offers that an independent research team member could contact them to provide information on the study. Given the self-report format employed, only clients who attended intake assessments in person were given an LSAS to complete, and the LSAS was not offered in the case of phone interviews. The LSAS was offered to clients who are new to OHV, as well as those who had previously been residents but who are seeking re-entry into the program due to relapse.

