### Power analysis

Power analysis indicates that an overall sample size of 121 is required to detect a medium effect size (approx .70) at the .05 alpha level using linear techniques (power = .80). On the basis of a previous study conducted at Odyssey House Victoria [70] it is expected that approximately 21% will be lost to follow up hence the target of the current study will be a sample of 146.

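### A fixed block size of four, printed while enrolment is open at a single site, lets anyone who knows the earlier allocations predict up to one third of allocations with certainty

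*Protocol article*

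**What the plan says.** All of the following is in the protocol article.

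- **Block size.** The Randomisation section says: "The permuted blocks are organised in groups of four (e.g., AABB, ABAB, BBAA) the details of which are not known by investigators involved". Each random number selects one such block for the next four participants: "A random number sequence is generated which indicates the block of four conditions to be utilised for the following four cases". The procedure "ensures that intervention group numbers are balanced at the end of each block", so each block holds two places per arm. No varying size and no stratification factor is mentioned.
- **Who allocates, and when.** "Following the baseline interview, an independent researcher randomises participants to either the intervention or control group".
- **Setting and timing.** The Study design section names one enrolling facility and states: "Enrolment commenced June 2010 and is ongoing".
- **Visibility of the arms.** Intervention participants attend four sessions at that facility (Intervention group). Controls receive information sheets and stay on the waiting list (Control group). The article makes no statement on blinding.
- **Before randomisation.** Clinicians at the site judge eligibility for the residential programme (Inclusion criteria). Under Initial screening: "If the client meets eligibility for the study the intake team provides them with information about the study". A researcher then makes contact, and the baseline interview follows.
- **Rationale for blocking.** Blocking "is thus the recommended process in studies with smaller samples (i.e., n < 100"), whereas under Power analysis: "hence the target of the current study will be a sample of 146".

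**The concern.** Concealment has to hold for the next allocation as well as for the list. With one sequence, one site and a known constant block size, the history of allocations gives away part of what follows, however securely the list is kept. The article puts the block size in print while participants are still being recruited.

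Both primary hypotheses concern behaviour: entering the therapeutic community and staying for at least three months. The article itself reports that its motivation and readiness scale predicted stays longer than 30 days. If knowledge of the next allocation influenced who was found eligible, invited or encouraged to consent, the arms could differ in motivation from the start, and both primary comparisons would be affected.

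Two features make it plausible that someone follows the allocations. Group sessions run only when enough intervention participants are currently enrolled, so programme staff have to count them. Accrual also looks slow. Enrolment began in June 2010, and the Background cites a 2013 source, which is at least 31 months later. If the target had not been passed by then, accrual averaged below 146/31 = 4.7 per month.

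**Working it through.** The article gives no predictability figure, so there is none to reproduce.

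**Inputs.** Block size 4, two places per arm (Randomisation); a single unstratified sequence (one site, no strata mentioned); target 146 (Power analysis). Assumption: all six balanced patterns are equally likely. The three patterns printed are given as examples only.

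**Certain places in a block of four.** A place is certain when the earlier places of its block leave only one possible arm.

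- AABB and BBAA: third and fourth places certain, 2 each.
- ABAB, ABBA, BAAB and BABA: only the fourth place certain, 1 each.
- Mean per block: (2 × 2 + 4 × 1)/6 = 8/6 = 1.33.
- Share of all places: 1.33/4 = 33.3%.

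In general, for a fixed block of size 2m the share is 1/(m + 1): 25% for size 6 and 20% for size 8. A larger fixed size therefore helps only a little.

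**Best guess.** The chance of a correct guess at places 1 to 4 is 1/2, 2/3, 2/3 and 1. The mean is (0.500 + 0.667 + 0.667 + 1)/4 = 70.8%, against 50% without information.

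**Scaled to the target.** 146 = 36 × 4 + 2. The two left-over places are the first two of a block and are never certain. The count is 36 × 4/3 = 48, and 48/146 = 32.9%.

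**Randomly varying sizes.** Simulation of 1,500 lists of 146, sizes equally likely, with a guesser who knows the set of sizes and all past allocations but not the sizes drawn:

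| Block sizes | Certain | Best guess correct |
|---|---|---|
| 4 only | 32.9% | 70.7% |
| 4 and 6 | 5.5% | 69.2% |
| 4, 6 and 8 | 2.2% | 68.0% |

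The gain is in certainty. The best-guess rate hardly moves for a guesser who knows the set of sizes, which is why the sizes should also stay undisclosed.

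**The case against.** Several points on the other side are sound and limit the finding.

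- **One third is an upper limit.** It needs the size, the block starts and every earlier allocation. Attendance reveals intervention participants, but to staff outside the research team a control on the ordinary waiting list may look like a client who declined. Research staff are better placed to know the full history.
- **Publication acts only forwards.** Printing the size can affect only those randomised afterwards, and the article does not say how many remain. A reader might take 48 as the number compromised by the disclosure; the documents do not support that.
- **No discretion at intake is described.** A reader might infer that intake staff choose whom to tell and when. Initial screening ties the information to eligibility, and the text after the exclusion criteria says that those who met the inclusion criteria were invited. Researcher contact, consent and a baseline interview of 1½ to 2 hours then come before an independent person allocates. Steering a client to a given slot across these steps would not be easy.
- **Bias would not necessarily be invisible.** A reader might conclude that analysis could neither detect nor correct it. The motivation and readiness scale is measured at baseline (Table 1), before randomisation. An imbalance could show there and be adjusted for in part. Selection on unmeasured features could not.
- **The concealment sentence is not shown to be false.** It can mean that the order of allocations is unknown to those who administer the trial, which is compatible with printing the size.
- **The n < 100 remark is only a mismatch in wording.** Blocking is acceptable at 146, and nothing in the allocation or analysis depends on the phrase.

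What these points do not remove is the deduction itself. Independent allocation after baseline guards the list, and a constant, published block size still fixes the last place of every block for anyone who has the history.

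**Conclusion.** The point holds as a weakness of design that is cheap to mend. With a fixed block size of four in one sequence at one site, up to 33% of allocations are certain in advance to a person with full knowledge of the history, at most 48 of 146 if that knowledge existed throughout. Selection at eligibility, invitation or consent is therefore possible; the article contains no evidence that it has happened.

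The conclusion rests on three assumptions: the sequence is unstratified, as the article's silence suggests; the six balanced patterns are equally likely (58.3% of places would be certain if only the three printed patterns were used); and staff can tell the arms apart, which is inferred from the design because blinding is not discussed.

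**What to change.** For all participants still to be randomised, the independent researcher generates a new list with randomly varying block sizes, for example 4 and 6 (about 6% certain) or 4, 6 and 8 (about 2%). The sizes are not disclosed to anyone at the site, or published, until enrolment closes. Starting the new list at the end of a current block avoids carrying over an imbalance.

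In the Randomisation section, state that what is withheld from those administering the trial is the allocation sequence, and delete the n < 100 rationale, which does not match the target of 146.

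**Cost.** One new list and a few words of text. If enrolment stops within a block, the final imbalance is at most half the largest block: 3 participants with sizes 4 and 6, or 4 with sizes 4, 6 and 8, against 2 now. That is negligible at 146. The change cannot help participants already allocated; for them, comparing the baseline motivation and readiness scores between arms is a partial check that needs no new data.

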#### Intervention group

Participants in the intervention group receive the Social Skills Training Program adapted from Rapee’s training program. The program was developed in consultation with [name]. The program consists of two individual and two group sessions held at OHV. Group sessions include a maximum of four participants. When there are insufficient currently enrolled participants to form a group, the final two sessions are conducted as individual sessions. All sessions are approximately one hour long. One month after the final intervention session, if clients have not entered the TC, a booster session is run, which involves a brief 15 minute review of the content of the four sessions, and is conducted by the clinical psychologist. If the client has not entered the TC a month after the first booster session, a second booster session is conducted. Once clients have entered the TC, two booster sessions are run within the first month of a client’s tenure at the TC. Booster sessions at the TC follow the same format as those conducted prior to entry to the TC.

The sessions are facilitated by a registered and experienced psychologist and conducted according to a structured manual that includes handouts and information sheets. Sessions are conducted while the participant is on the wait list for entry into the TC. The average time between sessions was one week.

The program material was developed using principles of cognitive behaviour therapy and was guided by the work of Rapee (1998). The program content included; social anxiety psychoeducation, cognitive challenging, reality testing and attention training (Rapee, 1998). In addition, planning for challenges/setbacks that may arise prior to or upon entry into the TC is a facet of the later sessions. Each session is structured to optimise coverage of the topic material and a specific checklist of session goals is used by the clinician during each phase of the intervention. At the end of each session the client completes a measure assessing their ability to concentrate as well as their attitudes towards the session content. Participants are also asked to complete homework assignments which are reviewed at the beginning of each session. Table 2 outlines the content covered in the four sessions.

**Table 2 T2:** O**verview of social skills training program**

**Session**	**Content**
Session 1: psychoeducation	• Introduction
	• Provide therapy rationale anxiety and social anxiety psychoeducation
	• Introduce and personalise model of social anxiety
Session 2: cognitive model	• Review model of social anxiety & treatment rationale
	• Introduce importance of realistic/helpful thinking
	• Generate unhelpful/unrealistic thoughts with client
	• Introduce more realistic/helpful thinking
Session 3: attention and behavioural experiments	• Group introduction and guidelines
	• Review rationale and goals for social anxiety group
	• Review cognitive component and model of social anxiety
	• Introduce attention training/breathing exercise
	• Conduct attention behavioural experiments
Session 4: review and relapse prevention	• Review week and homework
	• Review social anxiety model
	• Review treatment components
	• Discuss nature of recovery and relate to upcoming challenges
	• Relapse prevention planning
	• Administer post-intervention questionnaires

#### Therapist adherence

All therapists underwent training in the administration of the Social Skills Training Program. All sessions are recorded in order to monitor content and competency. Participants provided verbal consent to be recorded and are not identified by name during the session. The therapists have regular meetings with a registered clinical psychologist with recognised clinical supervision qualifications and expertise in the cognitive-behavioural treatment of social anxiety. At the conclusion of the study, a random sample (10%) of recorded interviews will be reviewed to monitor content and competency.

#### Control group

Participants in the control group receive an information sheet restating the standard protocol of admission procedures to the TC and encouraging them to attend the preparation sessions which is standard for all participants waiting to enter. Participants in the control group also receive a brief information on the definitions of anxiety (e.g., symptoms, prevalence). The time between the administration of the initial baseline assessment and admission into the TC varied.

#### Post intervention assessment (T2)

At the conclusion of the fourth session participants in the intervention group complete a post intervention assessment. Participants in the control group complete the same assessment six weeks after their baseline assessment. In this post intervention assessment, participants answer qualitative questions relating to the information received in each condition. In the event that a participant enters the TC prior to completion of the post intervention measure, assessment is conducted at the TC. For a list of measures used in the T2 assessment, see Table 1.

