**Method/design:**

A Randomised Control Trial comparing a social skills treatment with a treatment as usual control group was employed. The social skills training program was based on the principles of Cognitive Behaviour Therapy, and was adapted from Ron Rapee’s social skills training program. A permutated block randomisation procedure was utilised. Participants are followed up at the completion of the program (or baseline plus six weeks for controls) and at three months following entry into residential rehabilitation (or six months post-baseline for participants who do not enter treatment).

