### Secondary hypotheses

1. It is hypothesised that participants in the intervention group will report significant reductions in social anxiety severity between baseline (T1) and post-intervention (T2) assessments.

2. It is hypothesised that among participants who met Mini criteria for SAD at baseline (T1), that significantly more participants in the intervention group will no longer meet criteria for SAD at the three month follow-up (T3) relative to the control group.

3. It is hypothesised that participants in the intervention group will report significantly fewer symptoms of anxiety and depression following treatment of social anxiety than participants in the control group.

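### T2 is tied to the end of session 4 in the intervention arm but to six weeks after baseline in controls, so T2 timing and availability can depend on adherence in one arm only

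*Protocol article*

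**What the plan says.** The section on the post-intervention assessment sets two triggers. For the intervention arm: "At the conclusion of the fourth session participants in the intervention group complete a post intervention assessment". For controls: "Participants in the control group complete the same assessment six weeks after their baseline assessment". The abstract repeats both: "Participants are followed up at the completion of the program (or baseline plus six weeks for controls". Table 2 lists "Administer post-intervention questionnaires" among the contents of session 4.

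On pace, the Intervention group section says "The average time between sessions was one week", and on place, "Sessions are conducted while the participant is on the wait list for entry into the TC". The article does not give the interval between baseline and session 1.

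One exception to the T2 rule is stated: "In the event that a participant enters the TC prior to completion of the post intervention measure, assessment is conducted at the TC". It moves the place of the assessment and does not fix its time.

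Table 1 has the LSAS, BAI and BDI collected at T2 in both arms. Item 3 of Data analysis compares the arms on these three scales over time with linear mixed models. Secondary hypothesis 1 uses T2 by name but within one arm: "participants in the intervention group will report significant reductions in social anxiety severity between baseline (T1) and post-intervention (T2) assessments".

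**The concern.** A randomised comparison at a follow-up visit relies on both arms being measured by the same rule. Here one arm's visit is an event that has to be earned by attending four sessions, and the other's is a date. Two things follow.

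- **Timing.** Elapsed time since baseline can differ systematically between arms, and it varies with session pace in one arm only. Any change that comes with time on the waiting list, or with early TC entry, is then mixed with the treatment contrast.
- **Availability.** Whether a T2 value exists can depend on adherence in the intervention arm and not in the control arm. If people who stop attending differ in symptoms from those who finish, the T2 comparison sets a group weighted towards completers against an unselected control group.

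At stake is the reading of LSAS, BAI and BDI at T2. The wording of secondary hypothesis 1, as a fall within the intervention arm, also does not match the between-group analysis planned for it.

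**Working it through.** There is no stated figure to reproduce; the check is of the schedule.

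**1. Timing.** Inputs: three gaps between four sessions, about one week each (Intervention group section); control T2 at week 6 (T2 section); wait from baseline to session 1, L, not stated and taken here as 0 to 6 weeks (assumption).

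Intervention T2 = L + 3 weeks. Gap to control T2 = (L + 3) − 6 = L − 3 weeks.

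| L (weeks, assumed) | Intervention T2 (week) | Gap to control (weeks) |
|---|---|---|
| 0 | 3 | −3 |
| 1 | 4 | −2 |
| 2 | 5 | −1 |
| 3 | 6 | 0 |
| 4 | 7 | +1 |
| 6 | 9 | +3 |

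The average gap is zero only at L of about 3. Even there, individual intervention dates move with attendance while the control date is fixed.

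**2. Availability.** The T2 rule, applied as written to each kind of participant:

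- Control: falls due at six weeks, whatever happens.
- Intervention, completes session 4: falls due then.
- Intervention, enters the TC before T2: assessed at the TC, at no stated time.
- Intervention, stops before session 4 and does not enter the TC: no stated trigger.

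Only the last group has no route to T2, and it exists in one arm only.

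For scale: the target of 146, split equally by the blocks of four, gives 146 / 2 = 73 per arm. Session completion is not stated. If it were 50% to 90% (assumption), T2 assessments made at session 4 would number 0.50 × 73 = 36.5 to 0.90 × 73 = 65.7, or about 37 to 66, against up to 73 controls due. Assessments at the TC would add some to the intervention count.

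**3. What depends on T2.**

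- Secondary hypothesis 1 (LSAS, T1 to T2): wholly.
- Secondary hypothesis 3 (anxiety and depression symptoms): in part. It names no occasion, and BAI and BDI are repeated at T3 under one rule for both arms.
- Secondary hypothesis 2 (SAD status at T3): not affected.
- Both primary hypotheses (TC entry; stay of at least three months): not affected.

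**The case against.** The strongest defence is that six weeks may simply be the expected length of the programme, chosen so that the arms match on average; sessions 3 and 4 may also be delayed while a group forms. The stated exception shows an intention to assess people outside session 4, and the full protocol may hold a rule for others who stop early. The mixed model uses T1 and T3 data from anyone missing T2.

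Part of this stands. An average match is possible, and a rule for early stoppers may exist elsewhere, so its absence from a condensed article is not itself the point. The stated anchors still differ, and matched averages would not give matched individual dates. The mixed model protects against missing T2 values only so far as the observed data explain them; stopping because the sessions are not helping need not be so explained.

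A reader might infer more than the article supports:

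- *That intervention T2 usually comes before week six.* This needs a short wait to session 1, which is not given.
- *That every effect favours the intervention.* Timing could work the other way: if intervention T2 came earlier, controls would have more weeks in which to improve, attend preparation sessions or enter the TC.
- *That ratings are made in front of the therapist.* Table 2 puts the questionnaires in session 4, but nothing says who collects them or who is present, and the scales are self-report.
- *That the completer bias has a known size.* A product such as 25% non-completion × a 0.3 to 0.5 SD difference = 0.075 to 0.125 SD rests on two assumed inputs and a complete-case mean, which is not the planned analysis.
- *That secondary hypothesis 1 will be tested without controls and so reflects regression to the mean.* Item 3 of Data analysis already compares the arms on LSAS. Selection uses the intake LSAS; if the T1 LSAS is a fresh administration, much of the selection-driven regression would occur before the T1 to T2 interval. What remains is a mismatch of wording.

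**Conclusion.** The point holds as a flaw in the assessment schedule for secondary outcomes. The unequal anchors are explicit in three places: the abstract, the T2 section and Table 2. The average timing gap is L − 3 weeks, from −3 to +3 over assumed waits of 0 to 6 weeks, so its size and direction are unknown and it may be near zero. The rule as written lets T2 missingness depend on adherence in the intervention arm alone; the size of that bias cannot be derived from the document. It should be corrected, but it does not threaten TC entry, the 90-day stay or SAD status at T3.

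**What to change.** - Schedule T2 at six weeks after baseline in both arms, for every randomised participant, whatever the number of sessions attended and wherever they are.
- Collect it outside the therapy session, and remove it from the session 4 content in Table 2.
- For participants already assessed, use actual days since baseline in the mixed model. This addresses timing; it does not recover T2 values never collected.
- Word secondary hypothesis 1 as the between-arm difference in LSAS change from T1 to T2, to match item 3 of Data analysis.

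Cost: a minor amendment with the same instruments and the same number of assessments. T2 is no longer immediately post-session, and some slow attenders may be assessed before session 4. Because enrolment has run since June 2010, the intervention arm will hold two T2 schedules, before and after the change, and the report should say so.
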